## Abstract

**Background:**

Postpartum haemorrhage (PPH) causes about 70,000 maternal deaths every year. Tranexamic acid (TXA) is a life-saving treatment for women with PPH. Intravenous (IV) TXA reduces deaths due to PPH by one-third when given within 3 h of childbirth. Because TXA is more effective when given early and PPH usually occurs soon after childbirth, giving TXA just before childbirth might prevent PPH. Although several randomised trials have examined TXA for PPH prevention, the results are inconclusive. Because PPH only affects a small proportion of births, we need good evidence on the balance of benefits and harms before using TXA to prevent PPH. TXA is usually given by slow IV injection. However, recent research shows that TXA is well tolerated and rapidly absorbed after intramuscular (IM) injection, achieving therapeutic blood levels within minutes of injection.

**Methods:**

The I’M WOMAN trial is an international, multicentre, three-arm, randomised, double-blind, placebo-controlled trial to assess the effects of IM and IV TXA for the prevention of PPH in women with one or more risk factors for PPH giving birth vaginally or by caesarean section.

**Discussion:**

The trial will provide evidence of the benefits and harms of TXA for PPH prevention and the effects of the IM and IV routes of administration. The IM route should be as effective as the IV route for preventing bleeding. There may be fewer side effects with IM TXA because peak blood concentrations are lower than with the IV route. IM TXA also has practical advantages as it is quicker and simpler to administer. By avoiding the need for IV line insertion and a slow IV injection, IM administration would free up overstretched midwives and doctors to focus on looking after the mother and baby and expand access to timely TXA treatment.

**Trial registration:**

ClinicalTrials.gov NCT05562609. Registered on 3 October 2022. ISRCTN Registry ISRCTN12590098. Registered on 20 January 2023. Pan African Clinical Trial Registry PACTR202305473136570. Registered on 18 May 2023.

**Supplementary Information:**

The online version contains supplementary material available at 10.1186/s13063-023-07687-1.

## Administrative information

Note: The numbers in curly brackets in this protocol refer to the SPIRIT checklist item numbers. The order of the items has been modified to group similar items (see http://www.equator-network.org/reporting-guidelines/spirit-2013-statement-defining-standard-protocol-items-for-clinical-trials/).

## Introduction

### Background and rationale {6a}

Postpartum haemorrhage (PPH) is a leading cause of maternal death, responsible for about 70,000 deaths each year, worldwide [1, 2]. Tranexamic acid is a life-saving treatment for women with PPH. The WOMAN trial recruited over 20,000 women with PPH and found that intravenous (IV) tranexamic acid given soon after PPH onset reduces bleeding deaths by about one-third [3]. The World Health Organization (WHO) recommends that all women with PPH should receive tranexamic acid as a first-line treatment [4].

Tranexamic acid is more effective when given early, around the time bleeding starts. Every 15-min delay reduces the survival benefit by about 10% [5]. PPH usually occurs soon after childbirth. This suggests that giving tranexamic acid around the time of childbirth might prevent PPH. Although several clinical trials have examined the effectiveness of tranexamic acid for the prevention of PPH, the results are inconclusive [6–8]. Some bleeding-related outcomes were reduced by tranexamic acid but others were not, and in some trials, rates of nausea and vomiting were increased with intravenous tranexamic acid. Trials of tranexamic acid for PPH prevention give the trial treatment after cord clamping, which may be too late to prevent heavy bleeding in some women, as bleeding usually happens soon after childbirth [6–9].

Before using tranexamic acid to prevent PPH, we need good evidence of the benefits and any potential harms. Only a small proportion of births are complicated by PPH, and even when PPH does occur, most women survive. Assuming the risk of PPH is 5% and that tranexamic acid cuts this risk by 20%, we would need to treat 100 women to prevent one PPH. If there are no important harms, this might be acceptable, but if there are harms, the balance of benefits and harms will need careful consideration.

The ongoing WOMAN-2 trial is evaluating the effects of tranexamic acid at cord clamping for the prevention of PPH in women with moderate and severe anaemia having a vaginal birth [9]. Anaemic women have a much higher risk of PPH and are more likely to die from bleeding if PPH occurs [10–12]. If tranexamic acid is found to be effective, the balance of benefits and harms should be favourable in anaemic women.

The I’M WOMAN trial will evaluate the effects of tranexamic acid just before birth for the prevention of PPH in women with one or more risk factors for PPH giving birth vaginally or by caesarean section (CS). The results will deepen our understanding of the benefits and harms of tranexamic acid for PPH prevention. The trial will also evaluate the effect of the route of tranexamic acid administration. Tranexamic acid is usually given by slow IV injection. However, recent research shows that tranexamic acid is well tolerated and rapidly absorbed after intramuscular (IM) injection, achieving therapeutic blood concentrations within minutes of injection [13–17]. The intramuscular route should be as effective as the IV route for preventing bleeding.

There may be fewer side effects with IM tranexamic acid. In general, the risk of side effects is increased at high blood concentrations. Although tranexamic acid is rapidly absorbed after IM injection, reaching therapeutic concentrations within minutes, because of the absorption phase, peak blood concentrations are lower than with the IV route. By avoiding high blood concentrations, the IM route might cause fewer side effects (e.g. nausea, vomiting, dizziness). A better safety profile would be particularly important when using tranexamic acid for PPH prevention. The IM route would also have practical advantages. By avoiding the need for IV line insertion and a slow IV injection, it would free up overstretched midwives and doctors to focus on looking after the mother and baby.

Giving tranexamic acid before the bleeding becomes serious should maximise the benefits [5]. In vaginal births, bleeding can start after episiotomy or birth canal trauma as the baby is being born, so giving tranexamic acid at crowning should be more effective at preventing bleeding. In caesarean births, bleeding starts at the skin incision. Women having a CS have an increased risk of PPH, surgical blood loss can be substantial and there is strong evidence that preoperative tranexamic acid safely reduces surgical bleeding [18, 19]. Giving tranexamic acid just prior to skin incision should be most effective. A safety study of IV, IM and oral tranexamic acid in pregnant women having caesarean births found no evidence of maternal or neonatal adverse events. Tranexamic acid crosses the placenta but has a short half-life and is rapidly eliminated [20].

### Objectives {7}

The I’M WOMAN trial is a randomised, placebo-controlled trial to assess the effects of IM and IV tranexamic acid on PPH, adverse events and other important maternal health outcomes in women at increased risk of PPH. It will:Assess the effect of tranexamic acid on the risk of PPH and other bleeding-related outcomesCompare the effects of IM and IV tranexamic acid on the risk of PPHCompare the effects of IM and IV tranexamic acid on the risk of adverse events

### Trial design {8}

The I’M WOMAN trial is a parallel, randomised, double-blind, placebo-controlled, three-arm trial comparing the effects of tranexamic acid by the intramuscular and intravenous route with placebo in women with one or more risk factors for PPH giving birth vaginally or by CS. About 30,000 women will be allocated to receive either (a) 1 g of tranexamic acid as two 5-ml IM injections (100 mg/ml) and IV placebo (10 ml 0.9% sodium chloride), (b) 1 g of tranexamic acid by IV injection and two 5-ml IM placebo injections, or (c) matching placebo. An optimal, allocation ratio was used to maximise study power.

## Methods: participants, interventions, and outcomes

### Study setting {9}

We will conduct the trial in hospitals in Africa and South Asia where maternal mortality from PPH is high. Study sites will be listed in country-specific protocols and on the trial website (https://imwoman.lshtm.ac.uk/). Participating investigators and sites will be identified from the international network of health professionals that was established for the previous WOMAN trials. Before we start the trial, all relevant ethics and regulatory approvals will be in place. All principal investigators will be required to conduct the trial according to the protocol, Good Clinical Practice (GCP) guidelines, and other relevant regulations. We will only progress countries and sites able to obtain the necessary ethics and regulatory approvals in acceptable timeframes.

### Eligibility criteria {10}

For a woman to be eligible, the randomising clinician must be uncertain about whether to give tranexamic acid. If the clinician believes tranexamic acid is indicated based on the existing evidence, they should not randomise the woman into the trial. During the trial, if accumulating evidence from other trials clearly demonstrates that tranexamic acid prevents PPH with a favourable balance of benefits and harms, it would be unethical to randomise women to receive a placebo. If this happens, the placebo arm will be dropped, and we will continue to recruit women into the IM and IV TXA arms.

#### Inclusion criteria

Women thought to be aged 18 years or older admitted to hospital for a vaginal or caesarean birth and who are known to have one or more risk factors for PPH will be potentially eligible. A list of major risk factors is provided in Additional file 8. If accumulating trial data or newly published research suggests that a particular factor is not strongly associated with an increased risk of PPH, we will focus on recruiting women with other/additional risk factors.

#### Exclusion criteria

The fundamental eligibility criterion is the responsible doctor’s ‘uncertainty’ about whether to use tranexamic acid in a particular woman. Women should not be randomised if the responsible doctor believes that tranexamic acid is clearly indicated (e.g. you have given tranexamic acid within 12 h or plan to give tranexamic acid) or clearly contraindicated (e.g. known allergy to tranexamic acid).

Site eligibility will be assessed by collecting information on the experience and qualifications of the site staff, the number and route of births, and the incidence of PPH.

### Who will take informed consent? {26a}

If women can give fully informed consent, then information about the trial will be given and written consent will be obtained. An overview of the consent procedure is provided in Additional file 2.

First, a member of the site trial team will identify a potentially eligible woman and then approach the woman with the agreement of the primary carer. She will be given information about the trial (Additional file 4a) in a language she understands. The team member will explain the purpose of the trial that it does not involve any change to her birth plan and that she will receive all the usual interventions for preventing PPH and any other care she needs. The team member will explain that her participation is voluntary and that if she does not want to take part, we will respect her views and her decision will not affect her care. If she wants to take part, the team member will obtain written consent (Additional file 4). If she is unable to read or write, the participant information sheet will be read to her, and she will mark the consent form with a cross or thumbprint. In this case, an impartial witness must provide a signature confirming the mark. A copy of the information sheet and consent form will be given to the woman.

If the woman withdraws a previously given informed consent, data collected to the point of withdrawal of consent will be used as part of the analysis.

### Additional consent provisions for collection and use of participant data and biological specimens {26b}

N/A—no biological samples will be collected. Consent is obtained for the study staff to access participants’ medical records and for their anonymised data to be made freely available to the public.

### Interventions

#### Explanation for the choice of comparators {6b}

The I’M WOMAN trial has an active control (IV tranexamic acid) and a placebo control group. A three-arm trial with experimental treatment, active control and placebo group is considered the gold standard non-inferiority design by drug regulatory agencies and is strongly recommended by the International Council for Harmonisation of Technical Requirements for Pharmaceuticals for Human Use (ICH) and European Medicines Agency (EMA). The IM and IV tranexamic acid groups will be compared to assess non-inferiority. The placebo group will be compared to the tranexamic acid groups to confirm assay sensitivity and provide evidence about the effects of tranexamic acid on PPH prevention. While tranexamic acid is recommended for the treatment of PPH, it is not recommended for prevention, and the balance of benefits and risks in women giving birth remains uncertain based on existing evidence, so a placebo arm is ethically and scientifically justified.

#### Intervention description {11a}

##### Name and description of investigational medicinal product

Tranexamic acid is a synthetic derivative of the amino acid lysine that has an antifibrinolytic effect by blocking lysine binding sites on plasminogen, inhibiting the binding of plasminogen to fibrin [21]. It is sold under various trade names for the treatment of bleeding due to general or local fibrinolysis in adults and children from 1 year of age. It is a well-known drug with an excellent safety profile.

##### Drug administration and dosage schedule

Women will be randomly allocated to receive:

i)1 g tranexamic acid as 2 × 5 ml IM injections (100 mg/ml) and slow IV injection of placebo (1 × 10 ml of 0.9% sodium chloride)ii)1 g tranexamic acid by slow IV injection (1 × 10 ml) and 2 × 5 ml IM injections of placeboiii)Placebo by 1 × slow 10-ml IV injection and 2 × 5 ml IM injections

In caesarean births, the trial treatment will be given prior to skin incision, immediately after draping. In vaginal births, the trial treatment will be given at crowning. There should be no delay in administering the trial treatment. Both IM injections should be given first, then the IV injection.

For IM administration, the 1 g dose (10 ml) is divided into two 5-ml IM injections to reduce the injection volume (5 ml is considered the upper limit) [22]. The IM injections should be given into the vastus lateralis, ventrogluteal region or deltoid. The vastus lateralis is the preferred site because it is a large muscle with no major nerve structures [23].

Each treatment pack contains clearly labelled IM and IV treatments. The IM treatment kit has two ampoules each containing 500 mg (5 ml) of TXA or placebo and two syringe labels. Two sterile 5-ml syringes and two needles will be provided. The IV treatment kit has two ampoules each containing 500 mg (5 ml) of TXA or placebo and one syringe label. One sterile 10-ml syringe and one needle will be provided. Before administration of IM and IV treatments, the expiry dates should be checked and the randomisation number confirmed. Appropriately qualified staff will prepare and administer the IM treatment first then the IV treatment:

IM treatment: Open the IM treatment kit and draw up the contents of each ampoule into each 5-ml syringe using the needles provided. Administer the two 5-ml IM injections first.

IV treatment: Open the IV treatment kit and draw up the contents of both ampoules into one 10-ml syringe using the needle provided. Administer one 10-ml injection as a slow intravenous injection at a rate of about 1 ml/min using the usual IV administration procedure, after administering the two IM injections.

##### Benefits and harms

Early tranexamic acid treatment cuts the risk of bleeding deaths in PPH and trauma by a third [3, 24, 25]. Giving tranexamic acid just before surgery cuts blood loss and the need for a blood transfusion by about a third to one-quarter [19, 26]. Although women in the postpartum period have an increased risk of venous thrombosis [27], meta-analyses of randomised trials with tens of thousands of patients show no increase in thromboembolic events with tranexamic acid, even in women with PPH[3, 18, 24, 28, 29]. Because severe bleeding is a strong risk factor for thromboembolic events, tranexamic acid might even reduce the risk of thrombosis [30]. The risk of seizures is increased at high doses but not with the dosage used in this trial [29]. Tranexamic acid is mostly excreted within 12 h, and there should be no risk of accumulation with a single dose. Unpublished data indicates that tranexamic acid passes into breast milk at about 1/100 of the concentration in the maternal blood, so this is very unlikely to produce an effect in the infant [31]. There was no increase in adverse events in the infants of mothers who received tranexamic acid in the WOMAN trial. A randomised trial of IV, IM and oral tranexamic acid in 120 pregnant women found no serious adverse events in infant(s) despite some placental transfer [17].

Tranexamic acid is widely used and well tolerated. Potential adverse events reported by manufacturers to be associated with the use of tranexamic acid according to frequency are:Common (≥ 1/100 to < 1/10): diarrhoea, vomiting and nauseaUncommon (≥ 1/1000 to < 1/100): dermatitis allergicRare: hypersensitivity reactions including anaphylaxis, convulsions, visual disturbances including impaired colour vision, malaise with hypotension (generally following a too fast intravenous injection) and arterial or venous thrombosis

##### Investigator’s Brochure (IB)

Information about tranexamic acid will be detailed in an Investigator’s Brochure (IB). The IB should be reviewed annually. Studies that provide reliable information on the safety and efficacy of TXA that would help investigators assess the benefits and harms of TXA use will be included. Additionally, relevant information on updates from manufacturers of TXA will be included.

##### Preparation and labelling of medication to be used in the trial

Tranexamic acid has marketing authorisation in the UK and will be purchased from the open market. Marketing authorisation guarantees that drug manufacture and release comply with Good Manufacturing Practice (GMP). A GMP-certified manufacturer will prepare the matching placebo (sodium chloride 0.9%). Tranexamic acid and placebo ampoules and packaging will be identical. A clinical trial supplies company will conduct the blinding process and first-stage qualified person (QP) release. The blinding process involves replacing the manufacturer’s label with the clinical trial label. Other than the randomisation number (used for pack identification) and route of administration, the label text will be identical on all ampoules and comply with clinical trial requirements. To check the blinding, known tranexamic acid will be compared with blinded samples from a random set of treatment packs to determine which are tranexamic acid. The samples will then be un-blinded to confirm the accuracy of the labelling.

##### Drug storage and supply

When a site is ready to start, a box of treatment packs will be sent by the LSHTM CTU Global Health Trials Group or the in-country coordinating centre. Site stock level depends on the site’s average recruitment rate. Each time a participant is randomised and entered into the trial database, one pack from the site’s stock will be automatically deducted. When the stock reaches the site’s minimum level, the LSHTM CTU Global Health Trials Group or in-country coordinating centre will send another box (or boxes). Sites should send screening and entry data to the LSHTM CTU Global Health Trials Group as soon as possible after randomisation (ideally within 24 h). Sites must report all used, lost or damaged trial treatment packs to the LSHTM CTU Global Health Trials Group on a Drug Accountability Log.

At each site, the treatment packs will be stored securely in a place where they are always accessible to the trial team for randomisation. Although tranexamic acid is heat stable, it will be stored in a dry place where it is protected from excessive heat and freezing. The expiry date of the trial treatment will be printed on the ampoule label, the treatment pack and the drug box. When a batch of treatment packs is close to expiry, the principal investigator (PI)/trial pharmacist/delegate will be asked to arrange the destruction of affected packs and record this on a Drug Destruction Form (DDF). When a site is to be closed, the PI/trial pharmacist/delegate will arrange the destruction of all unused packs and return a completed DDF to the LSHTM CTU Global Health Trials Group to confirm disposal.

#### Criteria for discontinuing or modifying allocated interventions {11b}

If any contraindication to the trial treatment develops after randomisation, the trial treatment should be stopped.

#### Strategies to improve adherence to interventions {11c}

Site investigators should record the date and time of trial treatment administration. If the trial treatment is not given, or is given outside of the prescribed period, a reason should be given. Adherence to the protocol will be monitored, and we will record whether the full dose was given.

#### Relevant concomitant care permitted or prohibited during the trial {11d}

All women should receive the usual care in labour and after birth. There is no restriction on the use of concomitant medication. Participation will not result in any needed treatment being withheld. Women who develop PPH should be treated in the usual way at their hospital, which may include tranexamic acid.

#### Provisions for post-trial care {30}

Where a woman returns to the hospital for any adverse event associated with the trial, her travel costs will be reimbursed. LSHTM accepts the responsibility attached to its sponsorship of the trial and, as such, would be responsible for claims for any non-negligent harm suffered by anyone because of participation in this trial. The indemnity is renewed on an annual basis and LSHTM assures that it will continue renewal of the indemnity for the duration of this trial.

### Outcomes {12}

#### Primary outcome

The primary outcome is a clinical diagnosis of primary PPH. This may be an estimated blood loss of more than 500 ml in vaginal birth or more than 1000 ml in caesarean birth or any blood loss sufficient to compromise haemodynamic stability within 24 h of birth. Haemodynamic instability is based on clinical judgement and assessed using clinical signs (low systolic blood pressure, tachycardia, reduced urine output). The total estimated blood loss at the time of PPH diagnosis and presumed cause(s) of PPH will be recorded.

The true event rate of the primary outcome in the trial population is unknown. Interim analyses may indicate a lower-than-expected event rate, or new information may emerge that alters assumptions about the treatment effect, affecting the power of the study. To ensure the study has adequate power, prior to unblinding we will allow the primary outcome to be changed, with any changes set out in a statistical analysis plan.

#### Secondary outcomes

Specific to caesarean births:Intraoperative blood loss measured by quantifying the amount of blood in sponges and drapes used in surgery and blood loss from suctioning, excluding amniotic fluidSurgery durationIntraoperative whole blood/red cell transfusionPostoperative haemoglobin (Hb) or packed cell volume (PCV) up to the end of the second postoperative day, if known

All births:Postpartum blood loss measured using a calibrated obstetric drape starting immediately after vaginal birth or once the women are shifted to a bed in the observation area after CS surgery, for 1 h, or up to 2 h if bleeding continues after 1 h and the woman remains in bedBlood pressure and heart rate (lowest recorded blood pressure reading and associated heart rate) up to 24 h after birthInterventions for bleeding (uterotonics, non-trial TXA, blood transfusion, surgical and non-surgical interventions) within 24 h of birthNausea, vomiting and dizziness (when the calibrated drape is removed, the woman will be asked about her nausea, vomiting and dizziness during and since the birth) measured using the number of episodes and/or a score from 1 to 10Pain or adverse skin reactions at injection sites (when the calibrated drape is removed, each injection site will be inspected for local reactions and the woman will be asked about pain at her injection sites)Prespecified maternal adverse events up to discharge, death or 42 days postpartum (thromboembolic events, seizure, sepsis, organ dysfunction, coagulopathy)Other maternal adverse events up to discharge, death or 42 days postpartumMaternal mortality up to discharge, death or 42 days postpartum (all-cause, cause-specific, narrative)Length of hospital stayDays in intensive care unit (ICU)/high dependency unit (HDU)Transfer to another hospitalPrespecified neonatal outcomes up to discharge, death or 42 days (breastfeeding, intracranial haemorrhage, pulmonary haemorrhage, bruising, thromboembolic event, seizure, stillbirth/intrapartum death, neonatal death, cause of death, congenital and genetic abnormalities, adverse events)

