### Data collection and management

#### Plans for assessment and collection of outcomes {18a}

The local trial staff will collect consent, baseline, outcome, and adverse event data and send them to the LSHTM CTU Global Health Trials Group by entering them into the online trial database. All staff authorised to collect trial data will be trained in data collection procedures and GCP. The staff will first enter trial data onto paper case report forms (CRF) and then the trial database to allow easier data control. After completing the consent procedure, an entry form will be used to collect baseline data including the woman’s age, gestational age, parity, recent Hb or PCV if known, multiple pregnancy, planned route of birth, previous PPH, hypertensive disease, placental abnormality, antepartum haemorrhage, and any other PPH risk factors. We will also collect the date and time of randomisation and IM injection sites. We will follow up participants until discharge, death, or the end of the postnatal period (42 days), whichever occurs first, and trained staff will record outcome data onto an outcome form.

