#### Plans to promote participant retention and complete follow-up {18b}

Follow-up will take place in a hospital and should be minimal, so there is no need for strategies to increase retention. A woman can withdraw from the trial at any time. She may give her reason for withdrawal but she does not have to. If a woman withdraws from the trial, we will analyse data collected to the point of withdrawal, but no other data will be collected unless the woman gives permission. In all cases, we will respect the woman’s wishes. At discharge, women will be given an ‘alert card’ identifying them as an I’M WOMAN trial participant and asked to present this card to anyone providing medical care after discharge, up to day 42. The card will have instructions to ensure the AE reporting procedures are followed.

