### Adverse event reporting and harms {22}

Maternal and neonatal events which occur as a consequence of the CS or vaginal birth, events which commonly occur in this population independent of the trial treatment, events which are present before randomisation, and events which are recorded as study outcomes, do not need to be reported as adverse events. Although congenital and genetic abnormalities cannot be attributed to the trial treatment because it is given minutes before birth, we will record these on the outcome form.

Events recorded on the outcome form up to discharge, death, or day 42 (whichever is sooner) will be presented to the DMC for regular review, and so will not be reported using the adverse events (AE) reporting procedure. For maternal outcomes, this includes PPH, nausea, vomiting, dizziness, vascular occlusive events, seizure, infection, sepsis, organ dysfunction, and pain or adverse skin reaction at the injection site. For neonatal outcomes, this includes stillbirth/intrapartum death, neonatal death, intracranial and pulmonary haemorrhage, bruising, seizure, and vascular occlusive events.

Other medical events that fulfil the AE definition below will be reported up to 42 days after administration of trial treatment. If a woman is discharged before 42 days, outcome events after discharge and up to 42 days that fulfil the AE definition will be reported, including those on the outcome form. At discharge, women will be given an ‘alert card’ identifying them as an I’M WOMAN trial participant and asked to present this card to anyone providing medical care after discharge, up to day 42. The card will have instructions to ensure the AE reporting procedures are followed. A safety reporting overview is provided in Additional file 5.

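### Maternal and neonatal harm outcomes stop at discharge, so a post-discharge thrombosis, sepsis or maternal death that is reported by day 42 enters no listed outcome

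*Protocol article*

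**What the plan says.** Secondary outcomes, under Outcomes {12}, gives four groups of harm outcomes the same three end points: prespecified maternal events, other maternal adverse events, maternal mortality and neonatal outcomes. For the first group the wording is "Prespecified maternal adverse events up to discharge, death or 42 days postpartum", covering thromboembolic events, seizure, sepsis, organ dysfunction and coagulopathy.

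Two other sections settle how the end points combine. Plans for assessment and collection of outcomes {18a} follows women to "discharge, death, or the end of the postnatal period (42 days), whichever occurs first". Adverse event reporting and harms {22} says: "Events recorded on the outcome form up to discharge, death, or day 42 (whichever is sooner) will be presented to the DMC".

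The same safety section then covers the time after discharge: "outcome events after discharge and up to 42 days that fulfil the AE definition will be reported, including those on the outcome form". These events are found through an alert card. Under Plans to promote participant retention and complete follow-up {18b}, each woman is "asked to present this card to anyone providing medical care after discharge, up to day 42". That section also says: "Follow-up will take place in a hospital and should be minimal, so there is no need for strategies to increase retention". No scheduled contact after discharge is described.

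**The concern.** The sponsor uses 42 days for safety reporting and a shorter window, different for each woman, for the outcomes it lists. A thrombosis on day 10 in a woman who went home on day 2 would, if reported, be held in the trial's safety data but meet no outcome definition. Even the group for other maternal adverse events stops at discharge, although the safety section takes such reports to 42 days.

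This matters because the case for prophylaxis rests on harms. Background and rationale {6a} works an example with a 5% risk of PPH and a 20% reduction: 0.05 × 0.20 = 0.01, or 100 women treated to prevent one PPH. It calls this possibly acceptable only if there are no important harms. Objectives {7} includes comparing adverse events between the IM and IV routes, and Benefits and harms notes that the postpartum period itself carries a raised risk of venous thrombosis. For rare harms, leaving gathered events outside the defined comparison costs precision.

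**Working it through.** **What closes the window.** The limits are discharge, death and day 42, and the earliest applies ({18a} and {22}). For a woman discharged alive on day L < 42, the window is L days.

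**Does another provision bring later events in?**
- Other maternal adverse events: no, the same cut at discharge applies.
- Analysis by randomised group ({20a}): this says how data are presented. It does not lengthen an outcome's window.
- Composite strategy ({20a}): discharge is named among the intercurrent events that may preclude measurement of key outcomes. Nothing there says that a later thrombosis or death is counted.

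So as defined, post-discharge events fall outside every listed outcome.

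**Share of the 42 days covered.** Coverage = L/42. The article gives no length of stay, so L is an assumption.

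| Stay L (days) | Covered | Outside |
|---|---|---|
| 1 | 2.4% | 97.6% |
| 2 | 4.8% | 95.2% |
| 3 | 7.1% | 92.9% |
| 7 | 16.7% | 83.3% |
| 14 | 33.3% | 66.7% |
| 21 | 50.0% | 50.0% |

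More than half lies outside for any stay under 21 days.

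**Why this is not a share of events.** That share depends on how fast the hazard falls after birth, which the article does not give. If the hazard halves every h days and k = ln 2 / h, the share of 42-day events occurring by day L is (1 − e^(−kL)) / (1 − e^(−42k)). For an assumed 3-day stay:
- constant hazard: 7%
- h = 14 days: 16%
- h = 7 days: 26%
- h = 3 days: 50%

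A spread from 7% to 50% supports no single figure.

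**What fewer events would do to precision (illustration only).** Assume a 0.2% risk to day 42 and 20,000 women on tranexamic acid against 10,000 on placebo; the article does not state the allocation ratio. The 95% limits of the relative risk are RR multiplied and divided by exp(1.96 × √(1/e₁ + 1/e₀)).
- All events counted, 40 v 20: √(1/40 + 1/20) = 0.274, factor 1.71
- 25% counted, 10 v 5: √(1/10 + 1/5) = 0.548, factor 2.93
- 10% counted, 4 v 2: √(1/4 + 1/2) = 0.866, factor 5.46

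Passive reporting would recover some of the missing events, not all, so the gain from the fix lies somewhere between these cases.

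**The case against.** The best defence is that the design is deliberate: well-ascertained outcomes in hospital, with passive safety reporting afterwards. Benefits and harms says a single dose is mostly excreted within 12 h, so early events may be the most informative about the drug. The analysis plan is not shown, and tabulating adverse event reports by arm is commonly left to it. The DMC is also to receive data on adverse events that might be linked to tranexamic acid (Interim analyses {21b}).

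Much of this stands. A reader might infer that reported late events are dropped from every comparison by arm. The article does not show that; it shows only that they fall outside the listed outcomes. But the outcome window is something the article fixes rather than leaves open. Rapid excretion does not show that every resulting event is diagnosed before discharge, and the sponsor itself chose to gather events to day 42.

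A reader might also infer that the window favours tranexamic acid, on the reasoning that PPH lengthens the stay and so women on placebo are watched longer. The article does not support this: it gives no length of stay and no link between PPH and stay. Nor would such an effect be large. Take the planning rates of 11.5% and 8.625% (11.5% × 0.75) and assume a 1 to 3 day stay with 2 to 3 extra days after PPH. The ratio of mean windows, (base + 0.08625 × extra) / (base + 0.115 × extra), runs from 0.94 to 0.98. That is small beside a confidence factor of 1.71 even with every event counted. Length of stay is a post-randomisation outcome, so unequal observation is possible, but neither its presence nor its direction is established.

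**Conclusion.** The point holds as a gap in the outcome definitions. Prespecified maternal harms, other maternal adverse events, maternal mortality and neonatal outcomes end at discharge for any woman who leaves before day 42, while the same events after discharge are reported by another route and join no listed outcome. More than half of the 42-day period is outside the window for any stay under 21 days, and 93% to 98% for an assumed stay of 1 to 3 days. These are shares of time; the share of events is unknown.

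The primary outcome, confined to 24 h after birth, and the non-inferiority test are unaffected. The change is worth making because it strengthens a harm comparison that the trial says it needs, using data it already plans to gather. No claim of bias for or against tranexamic acid follows from the document.

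**What to change.** Add to Secondary outcomes a comparison by arm, to day 42 whatever the date of discharge, of thromboembolic events, seizure, sepsis, organ dysfunction, coagulopathy and maternal death. Count outcome-form events plus post-discharge adverse event reports, each event once. Treat neonatal events likewise where they are reported. Show this beside the in-hospital count, which remains the better-ascertained result.

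State with it that post-discharge capture relies on the alert card, so the day-42 counts are incomplete and must not be read as complete follow-up. Say also that ascertainment may still depend on length of stay: a woman in hospital is observed directly, while one at home is found only if she presents. Blinding should keep knowledge of treatment out of reporting but does not remove that dependence.

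The cost is an added outcome definition and a merge of two existing data sources, with a check for duplicates. No extra visit or contact is needed.
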